## Abstract

**Background:**

There is strong evidence suggesting that prebiotics and probiotics regulate gut microbiota, reducing inflammation and thereby potentially improving bone health status. Similarly, mechanistic evidence suggests that either low-impact or high-impact weight-bearing exercises improve body composition and consequently increase bone mineral density in individuals with osteoporosis and osteoarthritis.

**Objective:**

This study aims to investigate the effects of a synbiotic (probiotic+prebiotic) supplementation, an exercise intervention, or a combination of both on gut microbiota, inflammation, and bone biomarkers in postmenopausal women.

**Methods:**

A total of 160 postmenopausal women from New Zealand will be recruited and randomized to one of four interventions or treatments for 12 weeks: control, synbiotic supplementation, exercise intervention, or synbiotic supplementation and exercise. The primary outcome measure is the bone and joint biomarkers at baseline and week 12, whereas the gut microbiota profile and inflammatory cytokine measurements will serve as the secondary outcome measures at baseline and week 12. Baseline data and exercise history will be used to assess, allocate, and stratify participants into treatment measures.

**Results:**

Recruitment of participants will begin in September 2021, and the anticipated completion date is June 2022.

**Conclusions:**

To the best of our knowledge, this will be the first randomized controlled trial to analyze the effects of both a synbiotic supplement and an exercise intervention in postmenopausal women. On the basis of the results obtained, a combination of synbiotic supplements and exercise might serve as a noninvasive approach to manage and/or improve body composition and bone health in postmenopausal women.

**Trial Registration:**

Australian New Zealand Clinical Trials Registry ACTRN12620000998943p; https://www.anzctr.org.au/Trial/Registration/TrialReview.aspx?id=380336&isClinicalTrial=False

## Introduction

### Background

The global population is aging. The global incidence of postmenopausal osteoporosis is also increasing [1,2]. Postmenopausal osteoporosis is characterized by increased low-grade inflammation that contributes to low bone mass and degradation of bone mineral content, resulting in postmenopausal bone loss [3-5]. Elevated levels of proinflammatory cytokines (eg, interleukin [IL]–6, tumor necrosis factor [TNF]-α, IL-1, and receptor activator of nuclear factor kappa-Β ligand produced by activated T cells) induce osteoclast formation and activity during senescence [2,6]. Meanwhile, it is well recognized that conventional estrogen therapy in the form of hormone replacement therapy (HRT), such as estradiol implants, increases bone density by increasing the activity of osteoblasts, reducing bone resorption, and reducing inflammation [7-9]. However, the long-term use of HRT as an anabolic treatment and high doses of estrogen may not reduce the incidence of bone fracture [7] and are associated with long-term side effects. Therefore, nutritional interventions are safe and reliable for improving bone health status.

Studies have reported that changes in the gut microbiome can affect distant organs, including the bone and subsequently the development of osteoporosis [10]. Recent studies in rats and mice have suggested that the gut microbiome modulates immune status [11] as well as calcium absorption and molecular control of bone resorption [12-14]. Although studies have been conducted in animals, there are few studies in humans that have investigated the effects of pre- and probiotics on the gut microbiome and postmenopausal osteoporosis. Moreover, human gut microbiota is different from that of rodents, which is why many studies have faced limited success in their attempt to *humanize* the murine microbiota [15].

### Defining Osteoporosis and Its Significance

Osteoporosis is “characterized by low bone mass and microarchitectural deterioration of bone tissues, consequently increasing bone fragility and breakage” [16]. The term osteoporosis (*osteoun*) refers to *bone* and *pór* (*os*) to *passage+osis* [17]. The widely accepted clinical diagnostic criteria and intervention threshold are defined as bone mineral density (BMD) ≥2.5 SDs (T score ≤−2.5) below the mean value of a young reference at the lumbar spine, femur neck, or total hip bone in older men and postmenopausal women [18].

The vast burden of osteoporosis constitutes an increase in morbidity and mortality [19], loss of quality-adjusted life-years (QALYs) [20], and a continuous rise in the cost of health care services, such as clinics, nursing homes, and hospitals [21,22]. It is a growing global health concern, with the lifetime risk of sustaining any fracture at approximately 50% for women and 20% for men in individuals aged >50 years living in Western countries [23]. It has also been predicted to become an issue in developing countries as the aging population rises. The risk of fracture becomes higher as people age, especially in postmenopausal women [24].

In 2011, osteoporosis-related QALYs were found to be 11,249, with a projection of 13,205 and 15,176 for 2013 and 2020, respectively, because of fractures. The results also suggest that there are more QALYs for women (6028) than men (5221) [22].

As a global epidemic situation, the International Osteoporosis Foundation suggests that 33% of middle-aged women and 20% of men (aged >50 years) will have an osteoporotic fracture [25]. The disease constitutes an economic burden, particularly because of the high cost of treatment. Over US $300 million per annum is estimated to be spent on treating fractures, whereas the total cost is estimated at US $1.15 billion per annum in health costs, posing a heavy burden on health care service providers in New Zealand [20].

### Physical Activity

Physical activity is defined by the World Health Organization as any “bodily movement of the skeletal muscle, which requires energy expenditure” [26]. Physical activity enhances the composition and function of the human skeletal system. However, skeletal muscle performance also deteriorates with age [27], and a lack of exercise and physical activity has been linked to bone loss and ultimately osteoporosis [28]. Osteoporosis may cause falls that result in osteoporotic fractures in older women.

Previous studies, including Cochrane reviews, have reported the effects of physical activity on bone strength across the life spans [29] of children and adolescents [30] as well as women, especially postmenopausal women [31-33]. A study from Italy reported progressive resistance strength training of the lower limbs to be most effective for the neck of the femur BMD in patients with osteoporosis. In contrast, a multicomponent training program was suggested for a spine BMD intervention [34].

Neilson et al [35] have defined activity energy expenditure (AEE) as “a modifiable component of total energy expenditure (TEE) derived from both volitional and non-volitional activities.“ Total energy expenditure comprises multiple components, including physical activity energy expenditure, resting energy expenditure, and the thermic effect of food [36]. The impact of physical activity has been used to alleviate several obesity-related diseases and the overall burden of diseases in men and women alike [37].

### The Research

#### Overview

The gut microbiome could be a plausible target for the modulation of bone disorders in the aged, as it has been associated with the innate and adaptive immune system. Our previous study inquired into the association between the gut microbiome and bone health status based on the World Health Organization classification of osteoporosis among postmenopausal women [38]. The relationship between the composition and predictive function of gut microbiota in women and their bone density, classified into healthy and osteopenic or osteoporotic groups, was investigated. The findings of this recent study showed that α diversity of the microbial profiles differed based on the hip and femoral neck osteoporosis classifications. Meanwhile, β diversity principal component analysis by using the Bray-Curtis index showed differences based on femoral neck classifications. Positive correlations were observed between *Lactobacillus, Bacillus, Paenibacillus*, and *Geobacillus* (all from the phylum Firmicutes) and BMD at all sites. However, negative correlations were reported for *Bacteroides* and *Parabacteroides* and all BMD sites [39,40]. This finding agrees with previous reports that showed the importance of the *Lactobacillus* species in bone maintenance [14,41]. This result was similar to that of Li et al [42], who showed a negative correlation between *Bacteroides* and BMD.

In addition, a study conducted with ovariectomized rats showed the effects of probiotics, prebiotics, and synbiotics on mineral (calcium and phosphorus) metabolism and absorption. The effects were also observed in the form of higher *Bifidobacteria* and *Bacteroides* counts, lower pH, and reduced bone turnover. The intervention also resulted in a tendency toward lower bone alkaline phosphatase [43].

Therefore, modulation with a synbiotic food supplement and weight-bearing low-impact exercise (interventions) can be used to provide data that may contribute to improvements in osteoporotic patient care. This study will use a prospective stratified (by exercise history), randomized, 4-group experimental design with 2 major data collection points (baseline and week 12). Before randomization, participants will be stratified by exercise history (≥2 high-intensity exercise sessions per week and <2 sessions per week) using the International Physical Activity Questionnaire to ensure equal distribution among the 4 groups. However, all participants would be permitted to continue their usual physical activity regime.

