### Statistical Analyses

G*Power statistical software version 3.1.9.7 developed in Heinrich Heine University Düsseldorf was used to calculate the sample size to ensure 95% CI with an α value of .05. We require 36 participants for each group. The within-subject SD for the primary outcome variables CTx-I and P1NP with a correlation of 0.5 was used. The number of volunteers was increased to 40 to allow for a dropout rate of 10%.

The results will be presented as either percentages or mean differences. Normality tests will be assessed through Shapiro-Wilk tests carried out on each parameter before analysis. The conventional analysis of variance (ANOVA) for RCT analysis will be used, and ANOVA for repeated measures will be applied to study treatment differences, period effect, and the interaction between treatment and period (carryover effect). IBM SPSS version 25 and Minitab statistical software version 19 (Minitab LLC) will be used for statistical analyses. Comparing groups' pretest with Mann–Whitney U test and then comparing pre- and postintervention results with Wilcoxon is one option and transforming data into ranks and performing an analysis of covariance (or ANOVA) is another option. All analyses will be considered statistically significant at *P*≤.05.

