## Discussion

### Principal Findings

Degeneration of bone health in the form of osteoporosis, osteoporotic fractures, and osteoarthritis are major health care issues leading to a significant increase in morbidity and mortality in New Zealand and all over the world. Similarly, the growing number of patients with osteoporosis or osteoarthritis results in huge health care costs. The aim is to measure the effect of synbiotics, weight-bearing exercises (10,000 brisk walking steps per day), or a combination of both on gut microbiota, inflammation status, and bone health. This study is important for several reasons. This study is directed toward postmenopausal women who have experienced a rapid phase of bone loss 5 years postmenopause. The use of a synbiotic (a combination of probiotic and prebiotic) supplement is particularly novel in the modulation of the immune system, gut microbiota, and anti-inflammatory response. Studies are needed to measure the effects of synbiotic supplementation and weight-bearing exercise on gut microbiota, inflammatory status, and bone health. Randomization by exercise history will help eliminate the effects of the previous exercise regime for the study. There is a critical need for measures of bone turnover and not BMD only as a primary outcome.

The effects of probiotic or synbiotic supplementation on markers of inflammation have also been reported. A reduction in proinflammatory cytokines (eg, IL-1β, TNF-α, IL-6, and IL-8) and an increase in anti-inflammatory cytokines (IL-10 and IL-4) [44] were observed in response to these interventions. Similarly, studies have indicated the protective factors of probiotic supplementation [45] and exercise in bone metabolism and health [34]. Long-term participation in a relevant and targeted exercise regime is known to improve bone mechanical properties over time [46].

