### Strengths and Limitations of This Study

This study was designed as an RCT to account for exercise history, and the sample size and duration have been selected to ensure an adequately powered sample needed to detect clinically and statistically significant results. In this study, investigating the effects of both prebiotics and probiotics with and without weight-bearing exercise provides strong evidence for an RCT. The limitation of the study lies in the inability to extend the duration in terms of further follow-up.

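### Randomisation is stratified by exercise history, but the listed analysis terms leave the stratum out; the stratum cut and the activity exclusion also use different measures and need reconciling

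*Protocol article*

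**What the plan says.** The Overview (Introduction, The Research) describes a "prospective stratified (by exercise history), randomized, 4-group experimental design with 2 major data collection points (baseline and week 12"). The single stratification factor has two levels, taken from the International Physical Activity Questionnaire (IPAQ): "participants will be stratified by exercise history (≥2 high-intensity exercise sessions per week and <2 sessions per week"). The stated purpose is an even spread over the four groups. Participants may keep up their usual activity during the trial.

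The Statistical Analyses section says: "The conventional analysis of variance (ANOVA) for RCT analysis will be used". It goes on: "ANOVA for repeated measures will be applied to study treatment differences, period effect, and the interaction between treatment and period (carryover effect"). As an alternative it mentions that "transforming data into ranks and performing an analysis of covariance (or ANOVA) is another option", without naming a covariate.

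Elsewhere the article relies on the design to deal with exercise history. Principal Findings states: "Randomization by exercise history will help eliminate the effects of the previous exercise regime for the study". Strengths and Limitations states: "This study was designed as an RCT to account for exercise history".

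The Exclusion Criteria remove women who do an hour or more of moderate or vigorous activity on three or more days. They give no reference period and do not say whether the hour is per day or in total.

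**The concern.** Stratified randomisation forces the arms to be alike on the stratum, so the true sampling variance of a difference between arms no longer contains the variance between strata. A model without the stratum still counts that variance as error. The estimate stays unbiased, but its standard error is overstated and the test rejects too rarely. The precision that stratification was meant to buy is partly lost, in a trial that presents control of exercise history as a strength.

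The second point concerns the design rather than the model. Eligibility and stratification both depend on activity but measure it differently: one by sessions of high intensity, the other by minutes and days of moderate or vigorous activity. Some women who would fall in the upper stratum are ineligible and others are not. If few remain, the stratification does little.

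**Working it through.** **The plan's own figure.** 36 / (1 − 0.10) = 40 per group, and 4 × 40 = 160, so the dropout allowance is right. The 36 itself cannot be reproduced, because the article gives no effect size, SD value or power. It is used below only as the number analysed per arm.

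**Inputs.**
- From the document: four arms, 36 analysed per arm (144 in total), and α = 0.05 ("to ensure 95% CI with an α value of .05").
- Assumed: two-sided contrasts; strata fully balanced over arms; R², the share of variance in the analysed outcome that the stratum explains, at 5%, 10% and 20%. The document gives no value for R².

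**What R² refers to.** With two visits, the treatment × period test is the same as an ANOVA on the change from baseline to week 12. A stratum effect that is equal at both visits cancels there, so R² means the share of variance in *change*. In a plain ANOVA of week-12 values nothing cancels, and R² refers to those values. The article does not say which form its conventional ANOVA takes.

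**Standard error and type I error.**
- Overstatement of the SE without the stratum: 1/√(1 − R²).
- Two-arm type I error: 2 × [1 − Φ(1.96/√(1 − R²))].
- Four-arm type I error: approximately P(F(3,140) > 2.669/(1 − R²)), where 2.669 is the 5% critical value. A simulation of the four-arm F test (20,000 runs per setting; 4, 9 or 18 of 36 women per arm in the upper stratum) checks this.

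| R² | SE ratio | Two-arm type I | Four-arm, formula | Four-arm, simulated | Simulated with stratum term |
|---|---|---|---|---|---|
| 5% | 1.026 | 4.4% | 4.2% | 4.0–4.3% | 4.9–5.2% |
| 10% | 1.054 | 3.9% | 3.4% | 3.2–3.5% | 4.8–5.2% |
| 20% | 1.118 | 2.8% | 2.1% | 1.9–2.2% | 4.9–5.0% |

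At R² = 0 the simulated rate is 4.9–5.1% with or without the term.

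**Power.** Take a two-arm contrast with 80% power at 36 per arm when R² = 0. The standardised difference is d = (1.96 + 0.8416) × √(2/36) = 0.66, so d/√(2/36) = 2.80.
- Without the stratum: Φ[(2.80 − 1.96)/√(1 − R²)].
- With the stratum: Φ[2.80/√(1 − R²) − 1.96].

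| R² | Without | With | Points forgone |
|---|---|---|---|
| 5% | 0.806 | 0.820 | 1.4 |
| 10% | 0.812 | 0.840 | 2.8 |
| 20% | 0.827 | 0.879 | 5.2 |

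**How large an effect these R² values need.** If a share q of women is in the upper stratum, the difference between strata in within-stratum SDs is √[R²/(1 − R²) / (q(1 − q))]. With q = 50% this gives 0.46, 0.67 and 1.00 for the three R² values. With q = 10% it gives 0.76, 1.11 and 1.67. A small upper stratum and a high R² are therefore unlikely together.

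**Stratum against exclusion.** If the hour is per day, two kinds of women in the upper stratum stay eligible: those with two high-intensity sessions and no third qualifying day, and those with three or more sessions each under an hour. Women with three such sessions of an hour or more are excluded, as are women with two plus one long moderate day. The article gives no activity distribution, so the share removed is unknown. For illustration, suppose 30% of candidates are in the upper stratum, a fraction e of them is excluded, and nobody in the lower stratum is. The upper share among eligible women is then 0.30(1 − e)/(1 − 0.30e). For e = 20%, 50% and 80% this is 25.5%, 17.6% and 7.9%, or about 10, 7 and 3 women per arm of 40. The exclusion can also remove lower-stratum women through moderate activity, which would raise these shares.

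**The case against.** A covariate list is commonly left to an analysis plan, which is not shown here. Nothing in the article rules out adjustment, and it mentions a rank analysis of covariance. A reader might infer that the trial ignores or refuses the stratum; the text does not support that. What stands is that the section does name a model and its terms, and the one design factor is not among them.

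The harm is also mild. The error is on the conservative side, a stratum effect that is constant over time cancels in the change analysis, and the upper end of the assumed R² range needs large differences between strata. All of this stands and limits the size of the point. It does not remove it: the form of the conventional ANOVA is left open, and since women keep their usual activity, an effect of the stratum on change is possible.

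On the second point, a reader might infer that the exclusion removes most women who could be in the upper stratum, or that the cut lies at the edge of the eligible range. The document gives no activity figures, the rules overlap only in part, and two recognisable groups stay eligible. Nor are unequal strata a design error: a small stratum can still be balanced, and balance over the groups is the stated aim. Only the mismatch of definitions stands.

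**Conclusion.** The concern holds in a limited form. The listed analysis terms omit the factor on which the trial stratifies. If the stratum explains 5% to 20% of the variance in the analysed outcome, the four-arm test runs at about 4% down to 2% instead of 5%, and a two-arm contrast forgoes 1.4 to 5.2 points of power. These figures rest on the assumed R² and on full balance of the strata; if R² is near zero, nothing is lost. The omission costs precision, not validity.

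The stratum cut and the activity exclusion are not expressed on a common scale and partly overlap. The upper stratum may therefore be small, but its size cannot be established from the document.

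**What to change.** Include the randomisation stratum as a fixed factor in the primary model and say so in the Statistical Analyses section. For the repeated-measures form, include the stratum × period term, or equivalently put the stratum in a model for the change; a stratum main effect alone would not enter the treatment × period test. The cost is one degree of freedom out of 140, and no data beyond what the randomisation already uses.

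Before the first randomisation, reconcile the stratum definition in the Overview with the activity item in the Exclusion Criteria. State both in the same measure, give the reference period, and say whether the minutes are per day. Then check from screening data how many eligible women fall in each stratum. Which activity limits to use is for the investigators. The cost is a wording change and, if the stratum definition moves, a new randomisation list. The article describes recruitment as still to begin, so this can be done cleanly if it is done first.

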#### Research Questions

What are the effects of dietary interventions with synbiotic food supplements and weight-bearing exercises on bone metabolism, gut microbiota, and micronutrient or inflammation status in postmenopausal women? Do specific gut microbiota alterations moderate bone metabolism? How do individual differences in nutritional interventions affect gut microbiota and, subsequently, bone metabolism? Ultimately, can they be used as a treatment for postmenopausal osteoporosis? Our principal hypothesis is that improvement in bone health, gut microbiota, and inflammation status will be greater in participants randomized to the synbiotic+exercise group compared with participants in the control, synbiotic, or the exercise groups (Figure 1).

**Figure 1 figure1:**
[figure not shown]
Cartilage oligomeric matrix protein 4 Bones clinical study flowchart. BMD: bone mineral density; DXA: dual-energy x-ray absorptiometry; IPAQ: International Physical Activity Questionnaire.

#### Specific Aim

This study aims to examine whether supplementation of fermented milk or dairy (yogurt) with a synbiotic (probiotic+prebiotic) and weight-bearing low-impact exercise could be effective in achieving favorable changes in gut microbiota, inflammation status, and biochemical indexes of bone and joint metabolism.

Aim 1: to compare control, synbiotic, exercise, and synbiotic+exercise groups based on changes in the gut microbiota using 16S rDNA sequencing at baseline and week 12.

Aim 2: to compare control, synbiotic, exercise, and synbiotic+exercise groups based on changes in inflammation status (inflammatory cytokines) at baseline and week 12.

Aim 3: to compare control, synbiotic, exercise, and synbiotic+exercise groups based on changes in bone formation (procollagen type 1 N-terminal propeptide [P1NP]), resorption (cross-linked C-telopeptide of type 1 collagen [CTx-I]), and joint degradation (CTx-II/COMP [cartilage oligomeric matrix protein]) at baseline and week 12.

Aim 4: to compare control, synbiotic, exercise, and synbiotic+exercise groups based on changes in body composition (lean body mass and fat mass), total hip, femoral neck, and spine BMD (DXA [dual-energy x-ray absorptiometry]) at baseline and week 12.

